**4. Study design:**

**4.1 Principal and secondary outcome measures:**

The principal **outcome measures** are:

- The physical measurements at birth of the infants of obese mothers, that is, the ponderal index, sum of skinfold thickness measurements (skinfolds), and weight. These anthropometric indicators make possible a reliable estimate of the newborn's adiposity (fat mass).

The **secondary outcome measures** are:

- The levels of hormones involved in fetal growth regulation or reflecting the functioning of the fetal fat mass, measured in cord blood: C-peptide, IGF-1, leptin, adiponectin, and its different isoforms.

- The maternal metabolic indicators:

- the existence (or not) of diabetes and the modalities of its treatment
- fructosamine and HbA1c assays at delivery (reflecting mean maternal glycemic control during the weeks preceding the assay)
- maternal leptin and adiponectin levels at delivery, to characterize the maternal adipose tissue.

- Glycemic control in the newborn during the first days of life, assessed by monitoring capillary blood glucose.

-Perinatal events: mortality, malformations, obstetric trauma, perinatal asphyxia, respiratory distress, preterm delivery, and hypoglycemia.

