Screening for neonatal hypoglycemia is routinely performed for newborn infants of obese or diabetic mothers and in dystrophic newborns (birth weight at or below the 10th percentile or at or above the 90th percentile). Capillary blood glucose will be tested at 1 hour of life and then every 3 hours for at least 24 h or until there are 3 consecutive capillary blood glucose results > 3.3 mmol/L. The onset of hypoglycemia (< 2.5 mmol/L) will require appropriate management according to a pre-established protocol. The capillary blood glucose will be tested in the baby's crib, with a glucometer measuring the drop of blood from a small puncture in the heel. In normal-weight infants (birthweight ranging between the 10th and 90th percentiles) of mothers with a pregestational BMI in the normal range (18.5 to 24.9 kg/m2) with negative results from the diabetes screening, capillary blood glucose will not be tested routinely, consistent with standard practice. The episodes of clinically revealed hypoglycemia will be recorded.

Newborns with a neonatal disease requiring hospitalization will be managed, depending on its severity, in the neonatology unit at Pitié-Salpêtrière or in the neonatal intensive care unit or the neonatology department at Trousseau Hospital (Paris 12).

The newborns' weight curve and a specific follow-up of their food in the maternity ward will be recorded.

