**4.7 Data to be collected directly in the case report forms:**

- Maternal data collected at inclusion by questions about medical history and clinical examination
- Data from pregnancy follow-up:
- Monthly clinical data collection: weight, BP, proteinuria
- Results and dates of diabetes screening: fasting blood glucose, blood glucose values after oral glucose tolerance test 75 g during the second and third trimesters.
- Diabetes management: diet or insulin
- Results of ultrasound and fetal heart rate: fetal growth, malformations, vitality.
- Neonatal data:
- Apgar, cord pH
- Weight, height, head circumference
- Perinatal events: mortality, malformations, obstetric trauma, perinatal asphyxia, respiratory distress, preterm delivery, hypoglycemia
- Blood glucose values for the first 24 hours and beyond
- Hypoglycemia, blood glucose values
- Feeding during the neonatal period
- Laboratory data:
- for the mother: HbA1c, fructosamine, leptin, adiponectin
- for the newborn: cord blood glucose, C-peptide, IGF-1, leptin, adiponectin

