**10. Statistics and data management:**

**10.1 Description of the statistical methods to be used, including the timing of any planned interim analyses.**

The study design plans to include two groups of women, obese (BMI 30 kg/m2) and non-obese (18.5 ≤BMI< 25 kg/m2).

- *Principal statistical analyses*

The principal analysis will estimate the role of maternal obesity on the newborn's body composition. We will seek specially to differentiate the attributable portion associated with obesity from that associated with diabetes. The outcome measures will be the sum of the skinfold measurements, the ponderal index, and the birth weight. We will use a covariance analysis model. Besides obesity and diabetes (no diabetes, diabetes treated by diet only, and diabetes treated by insulin), the following potential confounding factors will be introduced into the model: maternal age, hypertension during pregnancy, smoking, parity, newborn's sex, geographic origin, paternal BMI, gestational age at birth, height of father and mother, and the study center. Fetal deaths will be excluded from the analysis.

- *Secondary analyses*

- The respective roles of obesity and diabetes on the functioning of the newborn's adipose tissue, assessed by the cord blood leptin and adiponectin assays, will be estimated by analysis of variance.

- The role of growth factors such as IGF-1 and insulin (the secretion of which will be estimated by the C-peptide assay) on the newborn's body composition will be estimated by linear regression.

- The relations between the maternal metabolic indicators (leptin, adiponectin, glycosylated hemoglobin, and fructosamine) and the newborn's fat mass (quantity and functioning) on the one hand, and the newborn's growth factors (C-peptide and IGF-1), on the other hand, will also be studied by linear regression.

- The rate of hypoglycemia developing in the 48 hours after the birth of infants of obese mothers will be estimated with its 95% confidence interval.

- The rates of perinatal events in the two groups will be compared with Fisher's exact test.

- *Calendar of analyses*

No interim analysis is planned. The analysis will take place 3 years after the study begins.

**10.2 Planned number of study subjects, and planned number of subjects at each study center, with its statistical justification.**

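### Hypoglycemia is among the perinatal events compared by Fisher's test, but only the obese group is fully tested for it, so the comparison mixes risk with detection

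*Protocol*

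**What the plan says.** Section 4.1 defines one secondary outcome as follows: "Perinatal events: mortality, malformations, obstetric trauma, perinatal asphyxia, respiratory distress, preterm delivery, and hypoglycemia". The case report form list in section 4.7 repeats the same seven items. The secondary analyses in section 10.1 then state: "The rates of perinatal events in the two groups will be compared with Fisher's exact test". Nothing in that sentence sets hypoglycemia aside.

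Section 4.4 says who is tested: "Screening for neonatal hypoglycemia is routinely performed for newborn infants of obese or diabetic mothers and in dystrophic newborns". Dystrophic means a birth weight at or below the 10th or at or above the 90th percentile. Testing starts at 1 hour of life and continues every 3 hours "for at least 24 h or until there are 3 consecutive capillary blood glucose results > 3.3 mmol/L". For normal-weight infants of normal-BMI mothers with negative diabetes screening, "capillary blood glucose will not be tested routinely, consistent with standard practice"; only episodes that show clinically are recorded.

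Section 10.1 also has a separate one-group analysis: "The rate of hypoglycemia developing in the 48 hours after the birth of infants of obese mothers will be estimated", with a 95% confidence interval.

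**The concern.** The only infants left without routine testing are in the control group. An episode without symptoms is found in an infant of an obese mother and missed in most infants of control mothers. An unadjusted Fisher test on the recorded rates cannot tell a higher risk from a more complete search. Whether a control infant is tested also depends partly on birth weight, which is a principal outcome of the study.

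The direction of the bias is known: it favours an excess in the obese group. Section 2.1 names the newborn's glucose metabolism as one of the consequences of obesity to be assessed, and notes that a single study has reported a higher hypoglycemia risk in these infants. A positive result produced by detection would look like confirmation. Glucose values not taken in control infants cannot be recovered later.

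A smaller point concerns the one-group rate. It is defined over 48 hours, while the stated minimum of testing is shorter.

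**Working it through.** **Step 1. Who is tested (section 4.4).**

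| Infant | Obese group | Control group |
| --- | --- | --- |
| Mother diabetic | tested | tested |
| Birth weight at or beyond 10th/90th percentile | tested | tested |
| Neither of these | tested | not tested; clinical episodes only |

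The groups differ only in the last row, and that row alone creates the bias.

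**Step 2. Number per group.** Section 10.2 gives 235 analysed and 309 included per group.
- Normal formula: 2 × (1.960 + 1.282)² / 0.3² = 233.5, so 234. The t-test version gives 234.5, so 235. The plan's figure is reproduced.
- Inflation for 24% not evaluable: 235 / 0.76 = 309.2, which agrees with 309 apart from rounding.
- Fisher's test does not need complete matched pairs. Applying only the 10% loss and 2% fetal deaths, 309 × 0.88 = 271.9, so I use 272 per group and check 235.

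**Step 3. Model.** These inputs are assumptions, because the protocol gives none of them:
- p: true risk, the same in both groups, 5%, 10% or 15%; detection is complete in the obese group.
- q: share of true control cases that fall in tested infants. If tested and untested controls have equal risk, q is the share tested. I take 25%: about 20% of a reference population lie at or beyond the two percentiles, plus some diabetic mothers. If cases concentrate in tested infants, I take 40-60%.
- c: share of untested control cases that show clinically, 10-25%.

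Detected share in controls: d = q + (1 − q) × c. Observed control rate = p × d. Apparent risk ratio = 1/d, where the true value is 1.

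Example with p = 10%, q = 25%, c = 10%: d = 0.25 + 0.75 × 0.10 = 0.325. The observed rates are 10% and 3.25%, and the ratio is 1/0.325 = 3.1.

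**Step 4. Rejection probability.** This is the sum of the two binomial probabilities over all tables with a two-sided Fisher p-value below 0.05, at 272 per group.

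| q | c | d | Apparent ratio | p = 5% | p = 10% | p = 15% |
| --- | --- | --- | --- | --- | --- | --- |
| 25% | 10% | 0.325 | 3.08 | 0.522 | 0.874 | 0.976 |
| 25% | 25% | 0.438 | 2.29 | 0.345 | 0.676 | 0.872 |
| 40% | 10% | 0.460 | 2.17 | 0.314 | 0.630 | 0.837 |
| 40% | 25% | 0.550 | 1.82 | 0.211 | 0.442 | 0.651 |
| 60% | 10% | 0.640 | 1.56 | 0.136 | 0.280 | 0.435 |
| 60% | 25% | 0.700 | 1.43 | 0.100 | 0.196 | 0.305 |
| equal ascertainment | – | 1 | 1.00 | 0.033 | 0.036 | 0.038 |

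At 235 per group the same scenarios run from 0.086 to 0.954, and equal ascertainment gives 0.031 to 0.037.

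The edges move with the inputs. Equal risk with 20% of controls tested and c = 10% gives a ratio of 1/0.28 = 3.6. With q = 60% and c = 50% it is 1/0.80 = 1.25, and rejection is 0.059 to 0.145 at 272 per group. Every scenario is above the equal-ascertainment level.

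**Step 5. The 48-hour window.** Tests at 1 hour and then every 3 hours fall at 1, 4 and 7 hours. Read literally, the alternative in section 4.4 lets testing end after three good values, at 7 hours. On the longer reading the minimum is 24 hours. Neither guarantees testing from 24 to 48 hours.

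**The case against.** The strongest reply is that no two-group test of hypoglycemia was meant. Section 10.1 gives hypoglycemia its own one-group estimate, section 3 names it apart from mortality and morbidity and speaks of estimation, and the neonatal morbidity definitions in section 4.4 leave it out. A statistical analysis plan, not shown here, could settle the matter. This may well be the intent, and it lowers the severity. But two lists in the protocol include hypoglycemia and no sentence removes it, so an analyst following the text would run the test.

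Several stronger readings are tempting and do not hold:
- A reader might infer that only infants of obese mothers are screened. Section 4.4 also screens control infants who are dystrophic or have diabetic mothers.
- A reader might infer that the comparison measures nothing but screening. It mixes screening with risk, in proportions that the protocol does not let one calculate.
- A reader might take the 87% rejection and ratio of 3.1 as the size of the problem. They assume equal risk in tested and untested controls. Screening is aimed at indications, so cases plausibly concentrate in those tested. The ratio is then 1.4 to 2.2 and rejection 10% to 84%.
- A reader might extend the point to the relation between newborn glucose course and cord hormones. Section 10.1 specifies no such analysis, so there is nothing to fault.

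On the 48 hours, the 24-hour figure is a minimum, section 4.7 collects glucose beyond the first day, and the 7-hour stop is one reading of a translated sentence. The two sections still need reconciling, but the point is minor.

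**Conclusion.** The concern holds in this limited form. As written, the plan tests hypoglycemia between groups although detection is complete in one group and selective in the other, and the bias is towards an excess in the obese group. With equal true risks of 5-15%, 25-60% of control cases in tested infants and 10-25% clinical detection of the rest, the false risk ratio is about 1.4 to 3. Fisher's test rejects in roughly 10% to over 90% of studies, against about 3.5% with equal ascertainment at a 10% true rate. The direction follows from the protocol alone; the size rests on these assumptions.

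Severity is moderate. Hypoglycemia is one of seven components of a secondary outcome. The principal outcomes, the sample size and the other six events are not affected.

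**What to change.** In section 10.1, state that hypoglycemia is excluded from the between-group Fisher comparison, and keep the planned rate with its 95% confidence interval in infants of obese mothers only. Any two-group figure should be descriptive, with the unequal testing stated beside it.

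Two substitute contrasts are less clean than they look. Comparing only clinically revealed episodes is affected by early testing and management in the obese group, which can pre-empt such episodes and bias the contrast the other way. Comparing only infants screened for the same indication conditions, for dystrophic infants, on birth weight, which is a study outcome.

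Also reconcile the 48-hour window in section 10.1 with the monitoring described in section 4.4, for example by stating the rate over the period actually monitored.

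The cost is a few sentences. Neonatal care and data collection do not change. The study gives up a two-group p-value that could not have been interpreted.

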**3. Study objectives:**

**The principal objective** of this project is to study whether the infants of obese mothers have differences at birth in body composition, assessed by weight and fat mass, compared with the infants of normal-weight mothers. We will focus especially on differentiating the role of maternal obesity from that of her diabetes.

**The secondary objectives** are tostudy:

- the differences in the functioning of adipose tissue of the newborn infants of obese, compared with non-obese, mothers, assessed by leptin and adiponectin assays;
- the relations between the different growth factors, such as IGF-1 and insulin, and the infant's birth weight and fat mass (because hemolysis is frequent in cord blood samples and insulin cannot be assayed in these conditions, insulin will be assessed by an assay of C-peptide, since they are present in equimolar quantities);
- the relations between the maternal metabolic indicators (leptin, adiponectin, glycosylated hemoglobin (HbA1c), fructosamine and blood glucose), the newborn's fat mass (quantity and functioning) and growth factors (C-peptide and IGF-1);
- the relations between the course of newborn's blood glucose level in the immediate postnatal period and the hormone concentrations measured in the umbilical cord blood (C-peptide, IGF-1, leptin, and adiponectin);
- estimation of the rates of perinatal mortality, morbidity, and hypoglycemia.

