The primary outcome measures of the study are the ponderal index and sum of skinfolds at birth. For the skinfolds, the study by Sewell et al (Am J Obstet gyneco) compared 76 overweight women (BMI ≥ 25 kg/m2) with 144 women with a BMI < 25 kg/m2. The skinfold thickness measurements at the tricipital and subscapular levels showed differences, respectively, of 0.4 mm (standard deviation of 0.95 mm) and 0.5 mm (SD 1.2), for an effect size for the two measurements of 0.42. No specific data for obese women have been presented. We have no study of the ponderal index from which we can base any hypothesis to calculate sample size. We would like to be able to show an effect size of at least 0.3 for this criterion.

To obtain a study power of 90% to demonstrate an effect size of 0.3, with an α (type 1) risk of 5%, the analysis should include a total of 470 women (235 in each of the two groups). The rate of loss to follow-up before delivery is estimated at 10%, that of fetal death at 2% (the fetal deaths will be excluded from the analyses of the anthropometric data). Because the groups are matched, we estimate the rate of women who cannot be evaluated for the principal analysis at 24%. It is therefore necessary to include 309 women in each group, for a total of 618 women.

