**10.3 Αlpha (type 1) risk**

All tests will be two-sided and will have threshold of significance of 5%.

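### The protocol lists three principal outcomes in sections 4.1 and 10.1 but two in 10.2, and tests each at 5% with no rule for reading them together

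*Protocol*

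**What the plan says.** Four places in the protocol bear on this point.

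- **Section 3.** The principal objective concerns "differences at birth in body composition, assessed by weight and fat mass", so weight is part of the main question.
- **Section 4.1.** The principal outcome measures are "the ponderal index, sum of skinfold thickness measurements (skinfolds), and weight": three outcomes.
- **Section 10.1, principal analyses.** "The outcome measures will be the sum of the skinfold measurements, the ponderal index, and the birth weight": the same three.
- **Section 10.2.** "The primary outcome measures of the study are the ponderal index and sum of skinfolds at birth": two outcomes, with weight left out.

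Section 10.3 then sets the level: "All tests will be two-sided and will have threshold of significance of 5" per cent. The protocol gives no test order, division of alpha or single lead outcome. It also does not say how many outcomes must reach significance.

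Section 10.2 builds the sample size on one comparison: "To obtain a study power of 90% to demonstrate an effect size of 0.3" with a 5% type 1 risk, which leads to 235 women per group. It reports earlier skinfold data "for an effect size for the two measurements of 0.42". It says that no study was available for the ponderal index and sets 0.3 as the target for that outcome. It gives no effect size for birth weight.

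**The concern.** The principal question is a single one: does body composition at birth differ between the two groups? It is to be answered through two or three outcomes, each tested at 5%. Unless the protocol says how the results combine, the outcome that carries the conclusion can be chosen after the data are seen. If one significant result is enough, the chance of a false conclusion exceeds 5%. If all must be significant, power depends on how many outcomes are counted and on effects that are not all stated.

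The contradiction over the number of outcomes makes this harder to settle later. A statistical analysis plan would inherit two lists and a flat 5% rule, and would have to overrule part of the protocol to resolve them.

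**Working it through.** **Inputs.** From section 10.2: 235 per group, effect size 0.3 for the ponderal index, 0.42 for skinfolds (0.4/0.95 = 0.421 and 0.5/1.2 = 0.417), power 90%, 24% not evaluable. From section 10.3: two-sided 5%. Assumed here: equal pairwise correlation between outcomes, varied from 0 to 0.9. All power figures are for a plain two-group comparison, as in section 10.2.

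**1. The plan's own figure.** n per group = 2(1.960 + 1.282)²/0.3² = 233.5, so 234 by the normal approximation. The noncentral t gives 0.8994 at 234 and 0.9007 at 235, so 235 is exact. Enrolment: 235/0.76 = 309.2, against 309 stated. The calculation is sound for one outcome.

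**2. Type 1 error if any one significant result suffices.** Under independence it is 1 − 0.95² = 9.75% for two outcomes and 1 − 0.95³ = 14.3% for three. With correlation (1,000,000 simulated normal draws):

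| Correlation | Two outcomes | Three outcomes |
|---|---|---|
| 0 | 9.7% | 14.2% |
| 0.5 | 9.1% | 12.5% |
| 0.7 | 8.4% | 10.9% |
| 0.9 | 7.1% | 8.4% |

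The error stays above 5% throughout.

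**3. Power of each outcome at 235 per group, two-sided 5%.** Skinfolds at 0.42: expected z = 0.42 × √(235/2) = 4.55, power 99.5%. Ponderal index at 0.3: expected z = 0.3 × √(235/2) = 3.25, power 90.1%. Birth weight: none can be derived, since no effect is given.

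**4. Power if all must be significant.**

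- Both section 10.2 outcomes at 0.42 and 0.3: under independence 0.995 × 0.901 = 0.896; by simulation about 90% for every correlation from 0 to 0.9.
- All three, with 0.3 assumed for weight: under independence 0.995 × 0.901 × 0.901 = 0.808; by simulation 81% at correlation 0, 83% at 0.5, 85% at 0.7 and 87% at 0.9.

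**5. Cost of controlling the error.** In a fixed order with skinfolds first, the ponderal index is claimed only if both tests succeed, so its power is the figure of about 90% in step 4. Holm's procedure on the two section 10.2 outcomes keeps about 99% for skinfolds and 90% for the ponderal index at those effects.

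**The case against.** The best defence has four parts.

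- **The study is observational.** It tests no treatment, plans no interim analysis and describes its principal analysis as estimation. That lowers the stakes. But the protocol also chooses significance tests and sizes itself on power to demonstrate an effect, so the question of joint error remains.
- **The outcomes overlap.** The ponderal index is computed from weight, and section 4.1 treats all three as indicators of adiposity. Independence is therefore the extreme case. This stands, and it is why the range matters more than the 14% end of it. Even at 0.9 the error is not back to 5%.
- **Section 10.3 sets a threshold per test.** It makes no family-wise claim, and each single test does meet its 5%. This also stands: the gap is that joint interpretation is unaddressed.
- **A multiplicity rule may sit in an analysis plan that is not shown.** That is possible, but it would not remove the conflicting outcome lists in the protocol.

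A reader might infer that one of the stated figures, 5% or 90%, must fail whichever success rule is used. The document does not support that. Requiring both section 10.2 outcomes holds the error at or below 5% and power at about 90%. Joint power as low as 73% for three outcomes arises only if 0.3 is applied to all of them, although the protocol quotes 0.42 for skinfolds and nothing for weight.

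**Conclusion.** The point holds in a limited form. The list of principal outcomes contradicts itself (three in sections 4.1 and 10.1, two in 10.2), and a flat 5% per test has no rule for joint interpretation. If any one result suffices, which the protocol neither states nor rules out, the family-wise error is about 8–14% for three outcomes or 7–10% for two, at assumed correlations of 0.9 down to 0.

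The 90% power is correct for one outcome at 0.3. It survives a requirement that both section 10.2 outcomes be significant, but not a requirement on all three if weight has an assumed effect of 0.3.

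The skinfold figure rests on 0.42, which comes from two single skinfold sites in overweight women, not from the four-site sum in obese women. It is the only skinfold effect the protocol offers.

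For an observational study this should be fixed, but it does not undermine the design.

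**What to change.** 1. Give the same principal outcomes in sections 4.1, 10.1 and 10.2, and say explicitly whether birth weight is among them.
2. Pre-specify family-wise control at 5% for those outcomes. One option is a fixed order, each at two-sided 5% and stopping at the first non-significant result: skinfold sum, ponderal index, birth weight. Holm's procedure is another.
3. State in section 10.2 the power of each outcome at 235 per group: about 99.5% for skinfolds at 0.42; about 90% for the ponderal index at 0.3, including when tested second; and no justified figure for birth weight. The 90% should be attached to the ponderal index, for which the 0.3 target was set, and not to whichever outcome is tested first.

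The cost is protocol wording, with no change to the 618 women planned. The drawback of a fixed order is that a later outcome cannot be claimed as confirmatory once an earlier one fails. It can still be reported with its estimate and confidence interval. The change should be made before the outcome data are examined.
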